#### Neurodevelopmental Observations

At term CPA, prior to the MRI/^1^H-MRS scan, an experienced neurodevelopmental therapist will record a 5-minute video of the infant to conduct a general movements assessment (GMA); a validated tool to noninvasively identify neurological issues, which may lead to cerebral palsy and other developmental disabilities (Spittle et al., 2018). Infants are placed in a supine position, with minimal clothing to allow freedom of movement. The video will be taken when the infant is fully alert, but not directly interacting with parents, healthcare providers, or receiving stimulus from any external sources.

At 3 months of CPA, we will request participants meet again with a developmental therapist. At this appointment, information about general health (including weight gain trajectories, feeding habits, and number of visits to a GP) will be recorded. A questionnaire about developmental milestones at 3 months of age (developed by the American Academy of Pediatrics) will be completed, as well as a Developmental Assessment of Young Children – Second Edition (DAYC-2) Test, a validated tool to identify children with possible developmental delay in the following domains: cognition, communication, social-emotional development, physical development, and adaptive behavior (Saleh and Smadi, 2017). A 5-minute video of the infant will also be recorded to allow for a second GMA to be completed.

### Sample and Data Analysis

#### Creatine, GAA, and Amino Acid Analysis

Creatine, GAA, arginine, glycine, and methionine will be measured in biological and nutrition samples *via* LC-MS/MS, according to the methods of (Tran et al., 2014), with slight modification (Tran et al., 2014). Briefly, a 6-mm hole punch of the “cell-free” plasma fraction of the Hemaspot™, 7 μl of urine, nutrition, or unlabeled standard, will be transferred to 1.5-ml safety lock Eppendorf tubes. 200 μl of methanol containing 10 μM 2,2-d_3_ Creatine (Sigma), 2.5 μM 2,2-d_2_ GAA (Sigma), and 2.5 μM of Labeled Amino Acid Standard Set A (Cambridge Isotope Laboratories Inc.) internal standards is added to each tube. Samples are sonicated for 5 min then vortexed for 20 min, before being centrifuged at 20,000× g for 5 min to pellet any precipitate or filter paper at the bottom of the tube. Supernatant (~170 μl) is transferred into 250-μl glass inserts placed in 2-ml glass vials (Agilent), followed by evaporation to complete dryness in a speed vacuum (Labconco, Kansas, MO, USA). After drying, the GAA and creatine carboxyl groups are derivatized (butylated) by the addition of 100 μl of 3 M butanol-HCL followed by incubation at 60°C for 30 min. After cooling to room temperature, excess butanol-HCL is evaporated under speed vacuum, after which the dry residue is resuspended in 200 μl of methanol: water (1:1 v/v) solution prior to LC-MS/MS analysis. The external standards consist of an eight sample serial dilution series of known concentration range (0–25 μM unlabeled GAA and 0–100 μM unlabeled creatine).

The LC-MS/MS system is composed of a vacuum degasser, binary pumps, column oven, and a temperature-controlled autosampler (Shimadzu, Nexera^®^ UPLC). This will be interfaced with a triple quadrupole mass spectrometer (Shimadzu, LCMS-8030) with electrospray ionization. The LC column (Agilent – 2.1 × 100 mm, 1.8 μm C18 Zorbax Eclipse plus) will be maintained at 30°C and elution carried out with a binary gradient mobile phase at a flow rate of 0.4 ml min^−1^. Mobile phase A will contain water with 0.1% formic acid, and mobile phase B will contain acetonitrile with 0.1% formic acid. The initial mobile phase composition will be 5% B, which is ramped linearly to 50% B over 6 min followed by a 2-min column wash at 100% B, with the column finally undergoing re-equilibration at 5% B for 3 min, thus yielding a total runtime of 11 min. The first 1 min is diverted to waste. The following ESI source conditions will be used: nebulizer gas flow rate 3 L min^−1^, desolvation line temperature at 250°C, heater block temperature 400°C, and drying gas flow rate of 15 L min^−1^. The MS will be operated in positive ionization with multiple reaction monitoring (MRM). The collision energy, Q1 and Q3 pre-bias voltages for the MRM transitions have been optimized using authentic creatine and GAA standards (SIGMA) *via* the automatic optimisation software (Labsolutions, Shimadzu), with optimal collision energy for creatine and GAA for the instrument being −15 eV. The precursor and product ion transitions were creatine 188.2–90 *m/z*, d_3_-Creatine 191.2–93 *m/z,* GAA 174.2–101.1 *m/z*, and d_2_-GAA 176.1–103.1 *m/z*. The sample and standard injection volume will be 5 μl. Peak areas will be determined using Lab solutions post-run browser software (Shimadzu). The creatine, GAA and amino acid concentrations of blood spots, urine, or nutrition samples will be calculated *via* linear regression of the serially diluted external (unlabeled) standard series using the isotope dilution technique.

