### Specific Aims

Compare cerebral, plasma, and urine creatine and GAA content between preterm and term infants at CPA.Describe preterm infant plasma and urine creatine and GAA concentrations and creatine:GAA ratio in the early postnatal period.Describe associations between cerebral creatine content, plasma, and urine creatine concentrations with maternal and infant characteristics at CPA.Compare creatine, GAA, arginine, glycine, and methionine concentrations in standard preterm nutrition, including TPN, preterm infant formulas, and breast milk.Determine whether dietary source of creatine (TPN, formula, or breast milk) is related to plasma or urine creatine concentrations in the early postnatal period.Describe associations between cerebral creatine content and blood and urine creatine concentrations with neurological outcomes (GMA, MRI, and DAYC-2) at CPA and at 3 months of corrected postnatal age.

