**Figure 1 fig1:**
[figure not shown]
Schematic representation of UNICORN sampling regime. Samples of neonatal blood, urine, and nutrition will be collected weekly or bi-weekly for the duration of the infants stay in hospital. Magnetic resonance imaging (MRI) and magnetic resonance spectroscopy (^1^H-MRS) will be performed at term corrected postnatal age (CPA). Infants will also undergo a general movements assessment (GMA) at CPA and at 3 months CPA. At the follow-up appointment at 3 months CPA, further neurological assessment will be completed using the Developmental Assessment of Young Children – Second Edition (DAYC-2) assessment tool.

**Blood sampling**: A blood sample will be collected biweekly. We will perform a heel prick to collect ~120 μl of whole blood using a capillary tube. All blood samples (cord, maternal, or infant) will be transferred to a Hemaspot™ SE blood separation device to facilitate collection of the cell-free blood fraction (referred to throughout as plasma for clarity) from a small volume of whole blood. Hemaspots are allowed to dry at room temperature before being stored at −20°C for future analysis.

**Urine sampling**: Around the same time as the blood collection, and on each alternate week, we will place some gauze into the infant’s nappy to facilitate a spot urine collection. Once obtained, this sample will be transferred to an Eppendorf tube and stored at −80°C for future analysis.

**Nutrition sampling**: A 200 μl sample of the nutrition (TNP, formula, and breast milk) being fed to each infant at the time of the blood and urine sampling will be collected. If in powdered form (formula), this will be reconstituted following standard practices. All samples will be transferred into an Eppendorf tube and stored at −80°C for future analysis.

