### Monitoring and Data Collection

The following covariates/potential confounders will be collected as part of this study:

Maternal characteristics and birth outcomes data:

Maternal ageComorbidities/factors (preeclampsia, gestational diabetes, chorioamnionitis, IVF)Country of birthDietary preferences (omnivorous, vegetarian, vegan)Smoking statusParityGravityMode of deliveryPlacental weight

Infant characteristics:

Gestational ageSexBirth weightEthnicityWeight and corrected postnatal age at the time of each sample collectionPresence of postnatal infection (blood culture positive and/or treatment with systemic antibiotics for >24 h) or necrotizing enterocolitis (Modified Bells Classification Grade II-III determined by the treating Pediatric Surgeon at time of diagnosis).Feeding schedule prior to each sample collection (<24 h)Venous hemoglobin and hematocrit count prior to blood sample collection

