### Statistical Analysis

Characteristics of the population will be tabulated, along with appropriate descriptive statistics of the study sample. Continuous data will be assessed for normality and expressed as means and standard deviations or median and interquartile range as appropriate. Categorical data will be expressed as counts and proportions. Average creatine content from nutrition per week for each baby in the early postnatal period will be calculated.

Differences in creatine and GAA measures (^1^H-MRS, plasma or urine) between infants born preterm and those born at term will be assessed at CPA using a t-test or Mann-Whitney U test as appropriate. The correlation between gestational age at birth and creatine and GAA measures at CPA will also be determined using a Spearman or Pearson correlation. Preterm infant plasma and urine creatine and GAA concentrations and creatine:GAA ratio in the early postnatal period will be described and plotted. Associations between cerebral creatine content, plasma and urine creatine concentrations with maternal, and infant characteristics at CPA will be determined using Spearman or Pearson correlations for continuous data (maternal age, gestational age, birth weight, parity, gravity, placental weight) or a t-test or Mann-Whitney U test for categorical data (infant sex, mode of delivery, maternal comorbidities, country of birth, ethnicity, and dietary preferences), as appropriate. Differences in creatine, GAA, and amino acid content of nutrition sources (TNP, formula or breast milk) will be determined using a one-way ANOVA or Kruskal-Wallis H test as appropriate. The association between creatine, GAA, and amino acid content of nutrition sources (TNP, formula or breast milk) and infant plasma and urine creatine at CPA will be assessed using a Spearman or Pearson correlation as appropriate. Finally, the association between cerebral creatine content, plasma creatine levels, and the ratio of plasma:cerebral creatine at CPA with GMA, MRI global injury, and DAYC-2 scores will be determined using linear regression at both CPA and at 3 months’ corrected postnatal age. Potential confounders such as gestational age and maternal and infant characteristics will be assessed, along with collinearity, prior to performing multivariable linear regression.

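### Urine creatine and GAA, a primary outcome, come from untimed spot samples with no dilution marker, and the ratio that cancels dilution is not planned for the analyses at term corrected age

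*Protocol article*

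**What the plan says.** All references are to the protocol article.

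- **Role of urine.** Primary Outcome Measures lists urine creatine and GAA levels from birth to discharge and at CPA. The overall aim at the end of the Introduction reads them as excreted creatine and GAA.
- **Sample.** Under Blood, Urine, and Nutrition Sampling, gauze is placed in the infant's "nappy to facilitate a spot urine collection". No timing of the void and no urine volume are described.
- **Assay.** "Creatine, GAA, arginine, glycine, and methionine will be measured in biological and nutrition samples". The same section then states that the "concentrations of blood spots, urine, or nutrition samples will be calculated" by regression on the external standards. No normalising step for urine follows.
- **Covariates.** Monitoring and Data Collection records weight, corrected age and recent feeding at each sample, but no urine output or other measure of hydration.
- **Comparison at CPA.** Statistical Analysis states: "Differences in creatine and GAA measures (^1^H-MRS, plasma or urine) between infants born preterm and those born at term will be assessed at CPA", by t-test or Mann-Whitney U test. Urine creatine at CPA is also related to gestational age, maternal and infant characteristics, and nutrition content.
- **Ratio.** Specific Aims: "Describe preterm infant plasma and urine creatine and GAA concentrations and creatine:GAA ratio in the early postnatal period". Statistical Analysis repeats this as description and plots only.

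**The concern.** The concentration in a spot urine is the amount of analyte excreted divided by the amount of water passed with it. Without a marker for the water, the concentration does not measure excretion, which is how the aim uses it.

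Dilution multiplies creatine and GAA in one sample by the same factor. If that factor varies only at random between infants, it widens the spread and weakens the preterm-term comparison and every correlation with urine creatine. If its mean differs between the groups, it shifts both analytes the same way. At CPA the term infants are newborn, while the preterm infants are weeks to months old and have a different feeding history, so equal mean dilution cannot be taken for granted.

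This matters for interpretation. The earlier urine study cited in the Introduction found higher GAA and lower creatine in preterm infants, so the two analytes moved in opposite directions. If preterm urine were more dilute, the creatine fall would look larger and the GAA rise smaller. If it were more concentrated, the reverse would hold.

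**Working it through.** The plan gives no urine SD, effect size or power, so there is no figure of its own to reproduce. The check has two parts.

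**1. What cancels dilution, and where.** Write the measured values in one sample as C·k (creatine) and G·k (GAA), with k the dilution factor.

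- Raw creatine and raw GAA both carry k. A 20% lower mean k in one group gives a 20% false difference in each.
- The ratio is (C·k)/(G·k) = C/G, so k drops out.
- The plan uses the ratio for the early description of preterm infants. At CPA the only planned urine quantities are creatine and GAA themselves.
- The brain signal is treated differently: the MRI/1H-MRS analysis section normalises metabolites to water. Haematocrit is recorded alongside blood samples. No counterpart exists for urine.

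**2. Illustration of the size.**

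From the document: 20 infants in each of five groups, hence 80 preterm and 20 term.

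Assumed, because the document gives no values: biological log-SD 0.4; dilution log-SD d = 0.3, 0.5 or 0.7, independent of biology; creatine truly 30% lower; two-sided 5% test.

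Formulas:
- Total log-SD = √(0.4² + d²)
- Effect = |ln 0.7| = 0.357
- Standard error = SD × √(1/80 + 1/20) = SD × 0.25
- Power from the noncentral t with 98 degrees of freedom and noncentrality 0.357/SE

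| Dilution log-SD | Total log-SD | Relative effective n (0.16/SD²) | Noncentrality | Power |
|---|---|---|---|---|
| 0 (perfect correction) | 0.40 | 100% | 3.57 | 94% |
| 0.3 | 0.50 | 64% | 2.85 | 81% |
| 0.5 | 0.64 | 39% | 2.23 | 60% |
| 0.7 | 0.81 | 25% | 1.77 | 42% |

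**If mean dilution differs.** Suppose true creatine is equal but mean dilution differs by 20%, so the false effect is |ln 0.8| = 0.223. With the same formulas the raw comparison is significant in 42%, 28% and 20% of studies at d = 0.3, 0.5 and 0.7, against a nominal 5%. The 20% is again an assumption.

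**What the ratio costs.** The log ratio also carries GAA variability. If both analytes have log-SD 0.4 and are independent, its SD is √(0.16 + 0.16) = 0.57. Power for a 30% fall in creatine alone is then 70% at 80 vs 20. That is below raw creatine at d = 0.3 (81%) and above it at d = 0.5 (60%). The ratio returns to 94% if the true log values correlate at 0.5, because its SD is then √(2 × 0.16 × 0.5) = 0.40.

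**The case against.** **Silence in a condensed article.** The assay is described in brief and follows a cited method with modification. The sentence on the preterm-term comparison speaks of measures, not concentrations, so urine normalisation might sit in a fuller document. This has some force. Against it, the article goes down to internal standards, ion transitions and the calculation of results, and it names every analyte. Creatinine is not among them, and a later analysis plan cannot normalise to something that was not measured.

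**Confounding is not shown.** A reader might infer that hydration and urine output are confounded with creatine excretion in this study. The document does not support that. It has no data on dilution, concentrating ability or evaporation from gauze by group, so neither the size nor the direction of a bias can be derived. What stands is added noise, and bias only on the condition that mean dilution differs.

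**The ratio is no full remedy.** A reader might conclude that the ratio should become the main urine result. That goes too far. It can lose power, as shown above. The Introduction also argues that both synthesising enzymes may be immature, and low activity of the first could lower GAA and creatine together. The ratio would hide such a parallel fall. This objection stands, and it limits the ratio to a supporting role.

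**Limited consequence.** The study is mainly descriptive, has no formal power calculation, and has cerebral and plasma creatine as further primary measures. The planned neurodevelopmental regression uses those two and not urine. This is true, and it keeps the point below the level of a fatal flaw.

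**Conclusion.** The point holds in a limited form. As written, the urine part of the primary outcome cannot separate excretion from dilution in the preterm-term comparison or the associations at CPA, and the one planned quantity that could help is not used there.

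The certain consequence is extra variability of unknown size. Bias in the same direction for both analytes is possible but conditional. The power loss from 94% to between 81% and 42% is an illustration: it rests on assumed SDs, an assumed 30% difference, full retention of the planned 80 and 20 infants, and perfect correction as the reference. It should not be read as an estimate for this study. The brain and plasma results are not affected. The change is worth making, and it is best made before the urine is assayed.

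**What to change.** 1. Measure a dilution marker in the urine already stored at −80°C: creatinine, or osmolality or specific gravity where volume allows.
2. For the preterm-term comparison and the associations at CPA, report dilution-normalised creatine and GAA beside the raw concentrations, and state in advance how the normalisation is done.
3. Extend the already planned creatine:GAA ratio, on the log scale, to the CPA analyses as a supporting urine measure, neither the sole nor the main one.
4. State the limits. The Introduction describes creatinine as a breakdown product of creatine and phosphocreatine, so a creatinine denominator is tied to the pool under study; osmolality or specific gravity avoids that link. The ratio carries the variability of both analytes and cannot show a parallel fall.

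**Cost.** The ratio needs no new data. Creatinine needs one further transition and standard in the existing LC-MS/MS run; osmolality or specific gravity needs a separate measurement and some sample volume. No extra sampling of infants is required.

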#### MRI/^1^H-MRS

MRI images will be scored according to the Kidokoro assessment tool (Kidokoro et al., 2013). Briefly, cerebral white matter, cortical gray matter, deep gray matter, and cerebellar abnormalities will be independently graded, and then the scores combined to calculate a single global brain injury score. The assessor will also note the presence of hemorrhage or cystic lesions throughout the brain. Hemorrhagic lesions will be graded using the Papile classification system (Papile et al., 1978) and cystic lesions characterized as periventricular leukomalacia, periventricular hemorrhagic infarction, or other (Barkovich, 2000).

Metabolic ratios from ^1^H-MRS spectra obtained with a TE of 135 ms will be calculated as previously described, with water used as an internal reference to normalize metabolite signal intensities (Koob et al., 2016).

#### Neurodevelopmental Observations

Motor function will be assessed by a developmental therapist trained in GMA and blinded to the clinical history of the infant. At term CPA, infants will be assessed on withering movements, which should include complex movements of the arms, legs, neck, and trunk. Poor withering movements include rigid or chaotic movements that lack fluency and coordination (Spittle et al., 2013) and are predictive of adverse neurodevelopmental outcomes. At 3 months of CPA, infants will be assessed on fidgety movements, which appear as small continual movements of limbs in all directions. Poor quality fidgety movements include larger amplitude and jerking movements (Spittle et al., 2013) and are again predictive of later outcomes. Infants will be scored independently at each postnatal age.

At 3-month CPA, infants’ development will also be reviewed using the DAYC-2 assessment tool (Saleh and Smadi, 2017). An overall score from the five domains tested (cognition, communication, social-emotional development, physical development, and adaptive behavior) will be generated for each infant. Collectively, MRI, GMA, and DAYC-2 scores will be used to assess the potential risk of poor neurological outcomes, based on early diagnosis strategies for cerebral palsy (Novak et al., 2017).

### Sample Size

This study will be the first observational study of creatine homeostasis in the preterm infant that encompasses plasma, urine, nutrition, and cerebral creatine measures across time. As the outcomes are mainly descriptive, no formal power calculation has been performed. However, ^1^H-MRS results reported by Koob et al. (2016) showed comparison of 13 preterm vs term infants allowed for measurement of a statistically significant (−17%) reduction in cerebral creatine content in preterm infants at CPA (tCr/H_2_0 × 10^−3^; term 0.12 ± 0.1 vs preterm 0.10 ± 0.1). This same study had a 20–25% failure rate in obtaining accurate MRI/^1^H-MRS measurements at CPA (Koob et al., 2016). Taking these data into consideration and a potential loss to follow-up at 3-month of 20%, we aim to capture 20 infants in each gestational group.

### Statistical Analysis

Characteristics of the population will be tabulated, along with appropriate descriptive statistics of the study sample. Continuous data will be assessed for normality and expressed as means and standard deviations or median and interquartile range as appropriate. Categorical data will be expressed as counts and proportions. Average creatine content from nutrition per week for each baby in the early postnatal period will be calculated.

Differences in creatine and GAA measures (^1^H-MRS, plasma or urine) between infants born preterm and those born at term will be assessed at CPA using a t-test or Mann-Whitney U test as appropriate. The correlation between gestational age at birth and creatine and GAA measures at CPA will also be determined using a Spearman or Pearson correlation. Preterm infant plasma and urine creatine and GAA concentrations and creatine:GAA ratio in the early postnatal period will be described and plotted. Associations between cerebral creatine content, plasma and urine creatine concentrations with maternal, and infant characteristics at CPA will be determined using Spearman or Pearson correlations for continuous data (maternal age, gestational age, birth weight, parity, gravity, placental weight) or a t-test or Mann-Whitney U test for categorical data (infant sex, mode of delivery, maternal comorbidities, country of birth, ethnicity, and dietary preferences), as appropriate. Differences in creatine, GAA, and amino acid content of nutrition sources (TNP, formula or breast milk) will be determined using a one-way ANOVA or Kruskal-Wallis H test as appropriate. The association between creatine, GAA, and amino acid content of nutrition sources (TNP, formula or breast milk) and infant plasma and urine creatine at CPA will be assessed using a Spearman or Pearson correlation as appropriate. Finally, the association between cerebral creatine content, plasma creatine levels, and the ratio of plasma:cerebral creatine at CPA with GMA, MRI global injury, and DAYC-2 scores will be determined using linear regression at both CPA and at 3 months’ corrected postnatal age. Potential confounders such as gestational age and maternal and infant characteristics will be assessed, along with collinearity, prior to performing multivariable linear regression.

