### Recruitment

We will recruit infants at gestational ages 23^+0^–26^+6^, 27^+0^–29^+6^, 30^+0^–32^+6^, 33^+0^–36^+6^, and 39^+0^–40^+6^ weeks. We will aim to capture 20 infants at each time point (with equal numbers of males and females). Eligible infants will be identified based on gestational age at delivery and consideration of inclusion and exclusion criteria. Pregnant women will be approached at presentation to Delivery Suite to discuss study participation. If consent is obtained, the mother and infant will be recruited to the study and the consulting obstetric, midwifery, neonatal, and nursing team advised of their involvement. Where pre-delivery consent is not obtained due to rapidity of labor and/or other clinical factors, cord blood will be collected preemptively, and retrospective consent and maternal blood sample sought within 24 h of delivery. If the parents do not wish to participate, the cord blood sample will be disposed of using routine clinical biological waste disposal systems and no further study samples collected.

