## Discussion

Both creatine and the creatine kinase circuit are critical for brain metabolism (Braissant et al., 2011). It is hypothesized that preterm infants will become creatine deplete in the early postnatal period, due to premature delivery from a maternal source of creatine *in utero,* limited capacity for endogenous synthesis postnatally, and a limited supply of creatine in newborn nutrition. This creatine depletion may alter cerebral creatine metabolism, contributing to or compounding the risk of neurological disability in this population.

We anticipate that preterm babies will have altered creatine homeostasis and reduced creatine accretion in the early postnatal period compared to an infant of the same postconceptional age. Whether or not relative creatine deficiency is associated with neurological deficit will be a secondary outcome of this study. As the results are mainly descriptive and a formal power calculation could not be completed, there is the possibility that sample size may become a limitation for some of the proposed analyses in this observational study. However, the data obtained will enable calculation of effect size for future studies. If our overall hypothesis is supported, this observational study will inform a future randomized control trial of infant dietary creatine supplementation following premature birth, with the aim of improving brain metabolism during a key stage of development and thereby reducing the burden of neurodevelopmental disability in this high-risk population.

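### The relation of gestational age to creatine at term corrected age is summarised only by a correlation coefficient, whose size depends partly on the recruitment quotas; a slope per week with stratum summaries would be more interpretable (minor).

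*Protocol article*

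**What the plan says.** Recruitment in the protocol article fixes the gestational bands: "We will recruit infants at gestational ages 23^+0^–26^+6^, 27^+0^–29^+6^, 30^+0^–32^+6^, 33^+0^–36^+6^, and 39^+0^–40^+6^ weeks". It also fixes the numbers: "We will aim to capture 20 infants at each time point". No infant is recruited from 37+0 to 38+6 weeks.

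Statistical Analysis plans two looks at gestation and the measures at term corrected age (CPA). The first compares preterm with term, where differences "between infants born preterm and those born at term will be assessed at CPA using a t-test or Mann-Whitney U test as appropriate". The second treats gestational age as continuous: "The correlation between gestational age at birth and creatine and GAA measures at CPA will also be determined using a Spearman or Pearson correlation". Gestational age appears again in the list of continuous characteristics to be correlated with creatine. No slope of creatine or GAA on gestational age is named. Linear regression is reserved for the neurological scores, where gestational age enters as a possible confounder: "Potential confounders such as gestational age and maternal and infant characteristics will be assessed, along with collinearity, prior to performing multivariable linear regression".

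The Discussion says that "the data obtained will enable calculation of effect size for future studies" and that, if the hypothesis is supported, "this observational study will inform a future randomized control trial of infant dietary creatine supplementation following premature birth".

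**The concern.** The investigators set the distribution of gestational age; it was not sampled from a population. A correlation coefficient combines three things: the change in creatine per week, the scatter around that change, and the spread of gestational age. Here the quotas determine the third. Two studies with identical biology but different band sizes would therefore report different values of r.

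The article also does not say whether the term band enters the correlation. That band lies at the far end of the scale, so the choice matters.

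What is at stake is how readable one descriptive result is. The Sample Size section calls the outcomes mainly descriptive, so interpretable magnitudes are a large part of what the study delivers. On its own, r does not say how much lower creatine is per week of earlier birth.

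**Working it through.** **Inputs.** The bands and the 20 per band come from Recruitment. Gestational age is taken as uniform within each band (an assumption), with bands 23–27, 27–30, 30–33, 33–37 and 39–41 weeks. The article states no expected r, slope or residual SD for this analysis, so there is no planned figure to reproduce; r = 0.30 and r = 0.50 are illustrative anchors. The natural mixes are assumptions, because the article gives no distribution of preterm births across the bands.

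**Step 1: variance of gestational age.** V = weighted mean of the within-band variances (width²/12) + weighted variance of the band midpoints.

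- Four preterm bands, equal weights: midpoints 25, 28.5, 31.5, 35; mean 30. Between = (25 + 2.25 + 2.25 + 25)/4 = 13.625. Within = (1.333 + 0.75 + 0.75 + 1.333)/4 = 1.042. V = 14.667, SD = 3.83 weeks.
- All five bands: mean 32. Between = (49 + 12.25 + 0.25 + 9 + 64)/5 = 26.9. Within = (4.167 + 0.333)/5 = 0.9. V = 27.8, SD = 5.27 weeks.
- Assumed preterm mix 10/15/20/55%: V = 12.76, SD = 3.57 weeks.
- Assumed preterm mix 5/5/10/80%: V = 8.20, SD = 2.86 weeks.

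**Step 2: r with slope b and residual SD s held fixed.** r = √(kV/(kV + 1)), where k = b²/s². Anchoring on r₀ in the four preterm bands gives k = [r₀²/(1 − r₀²)]/14.667. For r₀ = 0.50, k = 0.3333/14.667 = 0.02273.

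- Five bands: kV = 0.632; r = √(0.632/1.632) = 0.62.
- 10/15/20/55: kV = 0.290; r = √(0.290/1.290) = 0.47.
- 5/5/10/80: kV = 0.186; r = √(0.186/1.186) = 0.40.

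| Sample | SD (weeks) | r if 0.30 in quota preterm | r if 0.50 in quota preterm |
|---|---|---|---|
| Quota, four preterm bands | 3.83 | 0.30 | 0.50 |
| Quota, with term band | 5.27 | 0.40 | 0.62 |
| Assumed 10/15/20/55 | 3.57 | 0.28 | 0.47 |
| Assumed 5/5/10/80 | 2.86 | 0.23 | 0.40 |

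In r², adding the term band moves the middle case from 0.25 to 0.39. That comparison uses only the article's own bands and no outside population.

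**Step 3: simulation check.** With the slope set so that r = 0.50 in the full five-band sample (true slope 0.0948 per week), the simulated means were Pearson 0.504, Spearman 0.499 and slope 0.0953. In the four preterm bands alone they were 0.386, 0.380 and 0.0944. Spearman moves with the bands as Pearson does; the slope does not.

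**Step 4: limit of the slope.** Step 3 assumes a linear relation. Suppose instead that creatine rises by 1 unit per week up to 35 weeks and is then flat. The fitted linear slope is 0.95 in the quota preterm bands, 0.69 with term added, 0.91 under 10/15/20/55 and 0.88 under 5/5/10/80. With a plateau at 33 weeks the figures are 0.81, 0.54, 0.71 and 0.64.

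**The case against.** A reader might infer that this r is the effect size promised for future studies and that the promise therefore fails. The text does not support that. The Discussion refers to the data obtained in general, and those data also yield band means, SDs and a preterm–term difference. The study it goes on to name is a randomised supplementation trial, whose effect size would be a difference between arms.

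A reader might also infer that quota sampling invalidates the analysis. It does not: selecting on gestational age leaves the test of no association valid. Nor does the article say that r will be generalised to an unselected preterm population.

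Three further points narrow the matter:

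- A Pearson r can be converted to a slope as r × SD(creatine)/SD(gestational age) if both SDs are reported for the same infants. A Spearman coefficient cannot.
- The slope is independent of the mix only under linearity. The Introduction reports that spiny mouse kidney and liver lack the synthesising enzymes until a stage equivalent to about 35 human weeks, which makes a threshold plausible. Step 4 shows that the slope would then move too, though much less if it is confined to preterm infants.
- The shifts are modest against sampling error. With all 80 preterm infants evaluable, the 95% CI for r = 0.50 is tanh(0.549 ± 1.96/√77), or 0.31 to 0.65, which contains every value in the r = 0.50 column.

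It can also be said that slopes and intervals are details for an analysis plan that is not shown. That carries some weight, but the article does name a method for this relation, and it names regression for another aim. What stands is that a better summary of the same data is available at almost no cost.

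**Conclusion.** The point holds as a minor one. The continuous relation between gestational age and creatine or GAA at CPA is to be summarised only by a coefficient whose size depends partly on the recruitment quotas, and the article leaves open whether the term band is included. That single choice moves r from 0.50 to 0.62, or from 0.30 to 0.40, with identical slope and scatter. Against assumed natural preterm mixes, 0.50 would become 0.40 to 0.47; the milder mix changes it little.

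These figures rest on uniform gestational age within bands, a linear relation and constant scatter; the two mixes are illustrations. Only the magnitude is affected. The significance test, the preterm–term comparison and the Discussion's general statement about effect sizes are untouched.

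**What to change.** In Statistical Analysis, replace or supplement the correlation as follows:

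- For each creatine and GAA measure at CPA, fit a linear regression on gestational age at birth in weeks among preterm infants, and report the slope per week with its 95% CI. Use the log scale for plasma and urine if they are skewed.
- Give the mean and SD, or median and IQR, by gestational stratum including term, so that any departure from a straight line is visible.
- If r is kept, state whether term infants are included and label it as specific to the quota sample.

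The cost is a sentence or two of wording. It needs no new data, no change to recruitment and no method that the article does not already use elsewhere.
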